Due to their specific design, duodenoscopes are among the most complicated medical devices that require routine disinfection and reprocessing. This is mainly a result of the largely inaccessible elevator recess, which makes manual or automated cleansing and disinfection difficult, and therefore promotes persistent pathogenic colonization of the duodenoscope. As a result, there has always been concern over the potential for duodenoscopes to harbor and transmit pathogens between patients. Until relatively recently, this concern has been primarily theoretical. Infection transmission via endoscopy in general is extremely low, estimated to occur at a rate of less than 1 in 1 million procedures. Up until the early 1990s, endoscopy-related infections, while occurring rarely, had always been associated with breaches in published cleaning, disinfecting or drying protocols, or use of unapproved or defective devices or disinfectants.

More recently, however, there has been a sharp rise in the rate of duodenoscope-related infections. A 2016 report identified no less than 25 distinct outbreaks caused by contaminated duodenoscopes worldwide between 2012 and 2015 alone, affecting 250 patients, with at least a dozen of these having arisen from the United States. Alarming, a large proportion of these

outbreaks have been unrelated to any identifiable breaches in disinfection and reprocessing protocols, and there has been no apparent association with geographic location, duodenoscope manufacturer or model. This has called into question the robustness of traditional sterilization processes as well as traditional duodenoscope designs.

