More worrisome is the fact that duodenoscope-related infections and outbreaks are increasingly involving multidrug-resistant organisms (MDROs), which portend significantly higher rates of patient morbidity and mortality compared with traditional organisms. Among the most feared of these are the carbapenem-resistant Enterobacteriaceae (CRE), a family of gram-negative bacteria that has been repeatedly linked to duodenoscope-related infection transmission, and one that is resistant to almost all classes of available antibiotics. In order for a duodenoscope-related outbreak to occur, an index patient colonized with CRE or other pathogenic bacteria must undergo an ERCP procedure. Following this, the duodenoscope becomes colonized with the pathogen despite standard sterilization, and another patient who undergoes ERCP with the same duodenoscope then becomes colonized and/or infected. A 2018 nationwide European study demonstrated that nearly 40% of sites providing ERCP had one or more patient-ready duodenoscope(s) that were contaminated after standard processing, suggesting that our current disinfection protocols are inadequate when faced with this latest generation of MDROs. Pathogenic transmission in gastrointestinal endoscopy appears to be rising sharply in the last decade, with specific increases in the rates of MDRO transmission. The mortality rates associated with duodenoscope-related MDRO outbreaks can be devastating, with a 1-month mortality rate of over 20% reported in one American study.

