### **5.4. Randomization and Allocation**

Patients fulfilling the inclusion/exclusion criteria above will be randomized following consent in a 1:1 ratio. Permuted block randomization will be utilized in blocks of 8 patients. Allocation will be to one of two groups: 1) ERCP using ED34-i10T2 duodenoscope with DEC or 2) ERCP using a conventional duodenoscope (ED34-i10T). Confidential random number allocation will be accessed via a secure internet software. The study investigators, outcome adjudicators and patients will be blinded to allocation. The endoscopist will not be blinded. In cases where additional or alternate duodenoscope(s) is/are required to achieve the desired goal of the ERCP procedure, the choice(s) of device(s) will be left to the discretion of the endoscopist, regardless of the study arm to which the patient has been allocated.

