An exact test will be used to test the one-sided hypothesis that DEC is non-inferior to control duodenoscopes. Using a power of 80% with a one-sided alpha of 0.025, 236 subjects in each arm will be required, for a total of 472 patients. To compensate for possible loss of subjects due to attrition, an additional 10% of subjects will be enrolled, for a **total of 520 subjects**. It is therefore estimated that the study will require **9-12 months to complete**, based on the estimated volume of ERCPs and study enrolment rates at our center. No interim analyses will be planned.

The second co-primary outcome considers persistent bacterial contamination rate of the duodenoscopes after ERCP. A recent nation-wide analysis showed a persistent bacterial contamination rate of 22% after standard disinfection and reprocessing of duodenoscopes. This was common across multiple duodenoscope manufacturers and models. In particular, the Pentax ED34-i10T duodenoscope demonstrated a persistent contamination rate of 27%, though there was a small sample size of 11 assessing this group. No other published studies have reported specifically on reprocessing of ED34-i10T. However, real-world data from the FDA demonstrate a 9.3% total sample positivity rate among Pentax duodenoscopes. Furthermore, our preliminary data based on post-reprocessing bioluminescence scans demonstrate that 10% of ED34-i10T duodenoscopes require repeat re-processing due to counts representative of residual contamination.

Thus, when comparing persistent contamination between DEC and traditional duodenoscopes, we set an overall expected persistent contamination rate of 10% in the control arm. We propose that reduction in persistent bacterial contamination from 10% with ED34-i10T to 3% with DEC (a relative risk reduction of 67%) would be considered clinically significant. A hypothesis will therefore be tested that the persistent bacterial colonization rate with DEC will be 3% or lower:

$$H_0: P_{DEC} \geq P_{CON} \text{ (Equivalent or Inferior)} \quad H_1: P_{DEC} < P_{CON} \text{ (Superior)}$$

where  $P_{DEC}$  is the persistent contamination rate for DEC in this study,  $P_{CON}$  is the persistent contamination rate for traditionally designed duodenoscopes (control), and  $H_0$  and  $H_1$  are the null and alternate hypotheses, respectively.

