An exact test will be used to test the two-sided hypothesis that DEC is superior to control duodenoscopes in terms of persistent bacterial contamination. Using a power of 80% with a two-sided alpha of 0.05, 194 subjects in each arm will be required, for a total of 388 patients. To compensate for possible errors in sampling or loss of samples through transportation, an additional 10% of duodenoscopes will be sampled, for a **total of 426 subjects**. For the purposes

of the second co-primary objective of the study, the first 426 patients enrolled as part of the first co-primary objective will have their duodenoscopes sampled (213 from each arm). An anticipated 25% of the sample size will be recruited from Kingston.

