**B) Variables and data dictionary:**

| Variable Name | Description/ Definition                                            | Coding                             |
|-----------------------------|----------------------------------------------------------------------------------|--------------------------------------------------|
| study_id                    | unique study identifier                                                          | (whole number)                                   |
| scope_random                | study randomization and allocation                                               | 1 = scope design A; 2 = scope design B (blinded) |
| tech_outcome                | technical success, co-primary outcome #1 (non-inferiority)                       | 0 = unsuccessful; 1 = successful                 |
| micro_outcome               | persistent microbial contamination, co-primary outcome #2 (superiority)          | 0 = no event; 1 = event                          |
| ae_pancreatitis             | pancreatitis following ERCP (ascertained at 30-day follow-up)                    | 0 = no event; 1 = event                          |
| ae_bleeding                 | bleeding following ERCP (ascertained at 30-day follow-up)                        | 0 = no event; 1 = event                          |
| ae_perforation              | perforation following ERCP (ascertained at 30-day follow-up)                     | 0 = no event; 1 = event                          |
| ae_cholang                  | cholangitis following ERCP (ascertained at 30-day follow-up)                     | 0 = no event; 1 = event                          |
| ae_cardio_resp              | cardiorespiratory adverse event following ERCP (ascertained at 30-day follow-up) | 0 = no event; 1 = event                          |
| ae_death                    | death following ERCP (ascertained at 30-day follow-up)                           | 0 = no event; 1 = event                          |
| ice_duo_num                 | duodenoscope number                                                              | (one of several pre-specified numbers)           |
| ice_duo_ease_md             | ease of use of overall scope design, according to endoscopist/trainee            | (scale from 0 to 10)                             |

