### C) ANALYSIS

Two-tailed Fisher's exact tests and chi-squared tests will be used to compare proportions. Outcomes will be compared between groups in an intention-to-treat analysis without adjustment. Comparisons will be reported using relative risks (RRs) and numbers needed to treat (NNTs) along with their respective 95% confidence intervals (CIs).

*Post hoc* subgroup analyses will be performed on sex (female or male), age (<65 or ≥65 years), study site (Calgary or Kingston), procedural complexity (1-2 or 3-4), papilla status (native

papilla or prior sphincterotomy), disposition (inpatient or outpatient), biliary stent placement (present or none), and indication (suspected or confirmed malignancy or all others). All statistical analyses will be performed using RStudio version 1.2.1335 (Integrated Development Environment for R, Boston, USA).

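### The contamination co-primary is cultured repeatedly from a reused set of numbered duodenoscopes but is sized and tested as independent patients; positive within-scope correlation would make the interval too narrow and the power lower than 80%

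*Supplement*

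**What the plan says.** Patients "will be randomized following consent in a 1:1 ratio" (protocol 5.4). The second co-primary is the contamination result of the duodenoscope after reprocessing. Section 8.3 has the scope sampled and then returned to the endoscopy unit.

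Section 9.1 plans for 10% contamination in the control arm and 3% with DEC: "Using a power of 80% with a two-sided alpha of 0.05, 194 subjects in each arm will be required, for a total of 388 patients". It adds about 10% for lost samples: "the first 426 patients enrolled as part of the first co-primary objective will have their duodenoscopes sampled (213 from each arm". The named test is an exact test.

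The SAP (section A) puts 422 patients in the microbiology group. Section B lists the scope number, `ice_duo_num`, coded as "one of several pre-specified numbers". Section C names Fisher's exact and chi-squared tests and says: "Outcomes will be compared between groups in an intention-to-treat analysis without adjustment".

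Section 1.1 of the protocol explains why contamination should persist. The elevator recess "promotes persistent pathogenic colonization of the duodenoscope", and in an outbreak "the duodenoscope becomes colonized with the pathogen despite standard sterilization", after which the next patient is exposed to the same instrument.

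Neither the latest protocol nor the SAP mentions within-scope correlation, a design effect, a clustered model or an analysis by scope. SAP sections C and D give `ice_duo_num` no role.

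**The concern.** The unit counted is the patient, but the unit measured is the instrument. A fixed set of scopes supplies all the cultures, and the trial's rationale is that a contaminated scope can stay contaminated from one use to the next. If so, ten cultures of one scope carry less information than one culture from each of ten scopes.

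The two arms use different scope models, so a scope belongs largely to one arm. Randomizing patients therefore does not spread a bad instrument evenly across the arms. The intended conclusion concerns a scope design, so variation between instruments of the same design belongs in the standard error. At stake is the trial's only planned superiority claim.

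**Working it through.** **1. Reproduce the plan's figure.** Inputs from section 9.1: 10% v 3%, two-sided alpha 0.05, power 80%, 1:1. Pooled two-proportion formula with mean rate 0.065:

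n = [1.96·√(2·0.065·0.935) + 0.8416·√(0.10·0.90 + 0.03·0.97)]² / 0.07² = (0.6833 + 0.2904)² / 0.0049 = 193.5, so **194 per arm**, with 80.1% power.

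This matches exactly. The arithmetic is sound, but it takes all 388 results as independent.

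**2. Design effect.** With k scopes per arm and n cultures per arm, each scope gives m = n/k cultures, and DE = 1 + (m − 1)·ICC. The effective sample size is n/DE. Both k and ICC are **assumptions**. The SAP's 422 gives n = 211 per arm.

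- Mild end, 20 scopes, ICC 0.01: m = 10.55; DE = 1 + 9.55·0.01 = 1.10; effective n = 193.
- Severe end, 4 scopes, ICC 0.10: m = 52.75; DE = 1 + 51.75·0.10 = 6.18; effective n = 34.

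**3. Type I error of the planned test.** Beta-binomial simulation, 211 per arm, 10% true contamination in both arms, same ICC in both arms, two-sided Fisher at 0.05:

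| Scopes per arm | ICC | DE | Type I error |
|---|---|---|---|
| any | 0 | 1.00 | about 3.5% |
| 20 | 0.01 | 1.10 | 4.4% |
| 20 | 0.05 | 1.48 | about 8% |
| 20 | 0.10 | 1.95 | 13% |
| 8 | 0.02 | 1.51 | about 8% |
| 6 | 0.05 | 2.71 | 20% |
| 4 | 0.05 | 3.59 | 26% |
| 4 | 0.10 | 6.18 | 40% |

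About half of each figure is error in favour of DEC, so that part runs from about 2% to 20%.

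**4. Power at 194 per arm.** The formula in step 1, evaluated at the effective n:

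| Scopes per arm | ICC | DE | Effective n | Power |
|---|---|---|---|---|
| 20 | 0.01 | 1.09 | 178 | 77% |
| 20 | 0.05 | 1.44 | 135 | 65% |
| 20 | 0.10 | 1.87 | 104 | 53% |
| 10 | 0.01 | 1.18 | 164 | 73% |
| 10 | 0.05 | 1.92 | 101 | 52% |
| 10 | 0.10 | 2.84 | 68 | 38% |
| 5 | 0.01 | 1.38 | 141 | 66% |
| 5 | 0.05 | 2.89 | 67 | 38% |
| 5 | 0.10 | 4.78 | 41 | 25% |

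The interval widens by √DE, from √1.09 = 1.04 to √4.78 = 2.2 times.

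**5. Can more samples cure it?** The surplus helps little: 211/194 = 1.09, so it absorbs a design effect of about 1.09 and no more. With k fixed, setting n = 194·[1 + (n/k − 1)·ICC] gives n = 194(1 − ICC)/(1 − 194·ICC/k). For 5 scopes and ICC 0.01 this is 192.06/0.612, or 314 per arm. No number of samples suffices once ICC reaches k/194, which is 0.026 for 5 scopes and 0.052 for 10.

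**6. Illustration of one bad instrument (assumed figures).** Take six scopes per arm, all at 3% except one control scope at 50%. Each scope has about 35 cultures. Expected control positives are 35.2·0.50 + 175.8·0.03, about 23; DEC positives are 211·0.03, about 6. Fisher's test of 23/211 v 6/211 gives p = 0.0016.

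**The case against.** **The size is unknown.** This is correct. The SAP says several scopes and gives no count for either site, and no ICC is stated. With 20 scopes per arm and ICC 0.01, Fisher's conservatism keeps type I error under 5%. A reader might infer that the type I error is certainly inflated above 5%, or that each scope is cultured dozens of times. The documents support neither: both depend on the number of scopes and the correlation.

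**The mechanism is background.** Section 1.1 describes elevator-recess designs and outbreaks, not repeat cultures at these sites. Section 3.2 says that removing the cap takes away that recess, so correlation might arise mainly in the control arm, whereas the simulation uses the same ICC in both. If only the control arm is correlated, at equal event rates the design effect for the difference is the average of the two arms. For 5 scopes and ICC 0.05 that is (2.89 + 1)/2 = 1.95 rather than 2.89: smaller, but not negligible. Section 9.1 also mentions repeat reprocessing after bioluminescence scans, which could interrupt persistence if it continues during the trial. The documents do not say.

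**Scope is not strictly nested in arm.** A reader might assume that it is. Section 5.4 allows alternate duodenoscopes at the endoscopist's discretion, and the SAP records crossover (`ice_duo_cross`). Under intention-to-treat, one scope can contribute to both arms. Nesting is therefore predominant, not complete.

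**Patients were randomized, so a patient-level test is legitimate.** It could support a statement about the particular instruments used. It does not carry the uncertainty needed for a statement about the design.

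These points limit the magnitude. None supplies a reason to assume zero correlation, and none gives the recorded scope number a use.

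**Conclusion.** The concern stands in conditional form. Contamination is measured repeatedly on a reused set of scopes, while the sample size and the tests assume independence. For any positive within-scope correlation, the unadjusted interval is too narrow, the p-value tends to be too small, and power at 194 per arm is below the stated 80%.

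The direction follows from the plan's own rationale. The size rests on assumed scope counts, assumed ICCs, equal numbers of cultures per scope and a common ICC in both arms. Over the assumed ranges it runs from negligible to severe: design effect about 1.1 to 6.2 and two-sided type I error about 4% to 40%. The sponsor knows the number of scopes and can place the trial within that range.

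**What to change.** **SAP section C.** Prespecify one primary analysis of `micro_outcome` that accounts for `ice_duo_num`, chosen before unblinding from the known number of scopes. With enough scopes, this could be GEE clustered on scope with a small-sample-corrected variance. With few scopes, compare scope-level contamination proportions. Keep Fisher's test as an unadjusted sensitivity analysis. State which scope's sample counts when more than one was used, and how crossover samples are assigned. Report the number of scopes per arm, samples per scope and the ICC.

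**Protocol section 9.1.** State that the 80% power assumes zero within-scope correlation, and give power for a range of ICCs at the actual number of scopes.

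**Cost.** No new patients, samples or variables are needed. The interval will be wider and the power figure less favourable. With very few scopes the information is limited whatever the method: a two-sided permutation test of 3 v 3 scopes cannot go below 2/20 = 0.10, and 4 v 4 reaches only 2/70 = 0.029. With about 6 DEC events expected (3% of 211), a heavily parameterized model may also be unstable, which favours a simple prespecified choice.

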**A) Data groups:**

1. MICROBIOLOGY OUTCOME – co-primary outcome 1 (superiority outcome). N = 422 patients.
2. TECHNICAL OUTCOME – co-primary outcome 2 (non-inferiority outcome). N = 518 patients.
3. SAFETY OUTCOMES AND SECONDARY OUTCOMES. N = 518 patients.

**B) Variables and data dictionary:**

| Variable Name | Description/ Definition                                            | Coding                             |
|-----------------------------|----------------------------------------------------------------------------------|--------------------------------------------------|
| study_id                    | unique study identifier                                                          | (whole number)                                   |
| scope_random                | study randomization and allocation                                               | 1 = scope design A; 2 = scope design B (blinded) |
| tech_outcome                | technical success, co-primary outcome #1 (non-inferiority)                       | 0 = unsuccessful; 1 = successful                 |
| micro_outcome               | persistent microbial contamination, co-primary outcome #2 (superiority)          | 0 = no event; 1 = event                          |
| ae_pancreatitis             | pancreatitis following ERCP (ascertained at 30-day follow-up)                    | 0 = no event; 1 = event                          |
| ae_bleeding                 | bleeding following ERCP (ascertained at 30-day follow-up)                        | 0 = no event; 1 = event                          |
| ae_perforation              | perforation following ERCP (ascertained at 30-day follow-up)                     | 0 = no event; 1 = event                          |
| ae_cholang                  | cholangitis following ERCP (ascertained at 30-day follow-up)                     | 0 = no event; 1 = event                          |
| ae_cardio_resp              | cardiorespiratory adverse event following ERCP (ascertained at 30-day follow-up) | 0 = no event; 1 = event                          |
| ae_death                    | death following ERCP (ascertained at 30-day follow-up)                           | 0 = no event; 1 = event                          |
| ice_duo_num                 | duodenoscope number                                                              | (one of several pre-specified numbers)           |
| ice_duo_ease_md             | ease of use of overall scope design, according to endoscopist/trainee            | (scale from 0 to 10)                             |

|                  |                                                                                 |                                                                                                                                                                                                                                                                                                       |
|------------------|---------------------------------------------------------------------------------|-------------------------------------------------------------------------------------------------------------------------------------------------------------------------------------------------------------------------------------------------------------------------------------------------------|
| ice_duo_ease_rn  | ease of use of overall scope design, according to assisting/cleaning nurse      | (scale from 0 to 10)                                                                                                                                                                                                                                                                                  |
| ice_duo_cross    | crossover to alternate scope design/ study arm                                  | 0 = no crossover; 1 = crossover                                                                                                                                                                                                                                                                       |
| age              | patient age                                                                     | (continuous)                                                                                                                                                                                                                                                                                          |
| sex              | patient sex                                                                     | 1 = female; 2 = male                                                                                                                                                                                                                                                                                  |
| charlson         | Charlson comorbidity index                                                      | (whole number scale from 0 to 33)                                                                                                                                                                                                                                                                     |
| disposition      | patient disposition                                                             | 0 = outpatient; 1 = inpatient                                                                                                                                                                                                                                                                         |
| trainee          | trainee participation in ERCP                                                   | 0 = no trainee; 1 = trainee present                                                                                                                                                                                                                                                                   |
| indication       | indication for ERCP                                                             | 1 = ampullary obstruction or stricture; 2 = bile leak; 3 = benign or anastomotic biliary stricture; 4 = suspected or confirmed malignant biliary obstruction; 5 = cholangitis; 6 = suspected or confirmed biliary stones; 7 = repeat planned procedure including stent removal or exchange; 8 = other |
| complexity       | procedural complexity as defined by ASGE grade for complexity of ERCP           | 1 = Grade I; 2 = Grade II; 3 = Grade III; 4 = Grade IV                                                                                                                                                                                                                                                |
| ercp_prev        | previous ERCP                                                                   | 0 = no; 1 = yes                                                                                                                                                                                                                                                                                       |
| cbd_or_pd        | targetted duct for cannulation                                                  | 0 = common bile duct; 1 = pancreatic duct                                                                                                                                                                                                                                                             |
| scope_position   | scope position during ERCP                                                      | 1 = short; 2 = long                                                                                                                                                                                                                                                                                   |
| pre_cut          | pre-cut sphincterotomy performed (includes trans-pancreatic or supra-papillary) | 0 = no; 1 = yes                                                                                                                                                                                                                                                                                       |
| nk_papillotomy   | needle knife papillotomy performed                                              | 0 = no; 1 = yes                                                                                                                                                                                                                                                                                       |
| cbd_cannulation  | CBD cannulation achieved (only calculate among patients where cbd_or_pd = 0)    | 0 = no; 1 = yes                                                                                                                                                                                                                                                                                       |
| cannulation_time | cannulation time (only calculate among patients where cbd_cannulation = 1)      | (continuous)                                                                                                                                                                                                                                                                                          |
| sphinct          | formal sphincterotomy performed with sphincterotome                             | 0 = no; 1 = yes                                                                                                                                                                                                                                                                                       |
| balloon_sphinct  | balloon sphincteroplasty performed                                              | 0 = no; 1 = yes                                                                                                                                                                                                                                                                                       |
| cbd_stones       | CBD stones found                                                                | 0 = no; 1 = yes                                                                                                                                                                                                                                                                                       |

|                 |                                                               |                      |
|-----------------|---------------------------------------------------------------|----------------------|
| cbd_stricture   | CBD stricture found                                           | 0 = no; 1 = yes      |
| leak            | bile leak found                                               | 0 = no; 1 = yes      |
| cholangioscopy  | cholangioscopy performed                                      | 0 = no; 1 = yes      |
| biliary_stent   | biliary stent placed                                          | 0 = no; 1 = yes      |
| panc_stent      | pancreatic stent placed                                       | 0 = no; 1 = yes      |
| proc_time       | procedure time (from intubation to extubation)                | (continuous)         |
| gen_anesth      | general anesthesia or monitored anesthesia care performed     | 0 = no; 1 = yes      |
| midazolam       | amount of midazolam given (only calculate for gen_anesth = 0) | 0 = no; 1 = yes      |
| fentanyl        | amount of midazolam given (only calculate for gen_anesth = 0) | (continuous)         |
| glucagon        | amount of midazolam given (only calculate for gen_anesth = 0) | (continuous)         |
| diphenhydramine | amount of midazolam given (only calculate for gen_anesth = 0) | (continuous)         |
| indomethacin    | indomethacin administered to mitigate post-ERCP pancreatitis  | 0 = no; 1 = yes      |
| intra_aware     | intra-procedural awareness                                    | (scale from 0 to 10) |
| intra_discomf   | intra-procedural discomfort                                   | (scale from 0 to 10) |
| post_pain       | post-procedural abdominal pain                                | (scale from 0 to 10) |
| post_throat     | post-procedural throat pain                                   | (scale from 0 to 10) |
| post_nausea     | post-procedural nausea                                        | (scale from 0 to 10) |
| post_distend    | post-procedural distention                                    | (scale from 0 to 10) |

